**Figure 3 fig3:**
[figure not shown]
Examples of each of the four levels of training. **(A)** VR-MAT Level 1; One-hand drumming; **(B)** VR-MAT Level 2; Two-hand drumming, **(C)** VR-MAT Level 3; Two-hand drumming-reversed, **(D)** VR-MAT Level 4; Two-hand drumming-randomized.

#### VR-MAT behavioral data

2.3.1.

We will evaluate the VR-MAT performance four times [pre (day 1), mid1 (day 8), mid2 (day 15), and post (day 22) sessions]. We will obtain (1) the VR-MAT performance accuracy, which is defined as the number of matched strokes divided by the total number of strokes, and (2) the VR-MAT response time (RT), which is the time required for the matched strokes. No background music will be played during the evaluation sessions.

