## Abstract

Attention training is the primary step in the rehabilitation for patients with acquired brain injury (ABI). While active music performance has been reported to aid neural and functional recovery, its efficacy for patients with ABI remains uncertain due to methodological concerns. The purpose of the study is to develop a virtual reality-based music attention training (VR-MAT), which utilizes a visually guided, bilateral drumming in an immersive environment to train attention and executive functions. We also aims to examine the feasibility and effectiveness of the VR-MAT with a small sample size of participants (3–60 months after ABI, *N* = 20 approximately). Participants will be randomly assigned to either a waitlist control or music group, in which VR-MAT will take place five times weekly over 4 weeks (randomized crossover design). The evaluation of VR-MAT performance will include accuracy and response time in music responses. Neurocognitive outcome measures will be administered to quantify pre-post changes in attention, working memory, and executive functions. Additionally, functional near-infrared spectroscopy will be employed to explore the relationships between musical behavior, neurocognitive function, and neurophysiological responses.

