### Study design

2.1.

The present study will be conducted as an assessor-blinded, randomized, controlled trial with a crossover design at a rehabilitation hospital. Participants will be randomly allocated to either the treatment sequence: VR-MAT first and second with conventional cognitive training (CT) (VC group), or in the opposite order (CV group) with an allocation ratio of 1:1 using a computer-generated randomization table. The crossover design is selected because the participants need to serve as their own control group to minimize confounding effects on cognition, which might be markedly affected by a person’s traits, which is not intended by the intervention. In addition, it might be beneficial for the statistical efficiency of this pilot trial, in which VR-MAT had not been attempted for patients with ABI.

Each VR-MAT or CT training period will last 4 weeks with five 30-min intervention sessions per week, resulting in a total of 20 sessions. Therefore, each participant will have received a total of 40 sessions of the intervention, comprising 20 sessions of VR-MAT and 20 sessions of CT. The randomized group assignments were concealed in consecutively numbered sealed opaque envelopes placed in a plastic container. The allocated group will then be determined by the sequential opening of the envelopes after obtaining written informed consent from the participants. Participants will receive a conventional inpatient rehabilitation program (1 h of physical therapy or 30 min of occupational therapy); however, they will not receive a cognitive intervention. Outcome measurements will be performed by a researcher blinded to the group assignment.

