### Outcome measurement

2.5.

Baseline demographic characteristics, including sex, age, diagnosis of ABI, duration after ABI, side of brain lesion, and education, will be collected. Additionally, neuropsychological outcomes will be measured for each participant at baseline, after 20 sessions (4 weeks), and after 40 sessions of intervention (after 20 sessions of alternative intervention; 8 weeks) by a blinded neuropsychologist. We will collect data on neuropsychological outcomes in two ways: global cognitive function and executive function, which are specific targets of VR-MAT. All of the cognitive function tests will be administered in Korean. Additionally, we will obtain VR-MAT behavioral data, which is previously explained, and functional infrared spectroscopy (fNIRS) data (Table 1).

**Table 1 tab1:** List of outcome measurements.

Global neuropsychological assessment	Mini-mental status examination (MMSE)
Clinical dementia rating (CDR)
Global deterioration scale (GDS)
Subjective memory complaint questionnaires (SMCQ)
Executive function assessment	Trail making test (TMT)
	TMT-black & white (TMT-B&W)
	Attention-switching Task (AST)
	Stop signal task (SST)
	Spatial working memory (SWM)
VR-MAT behavioral measures	VR-MAT response time
	VR-MAT accuracy
Functional near-infrared spectroscopy	Oxygenated hemoglobin
	Deoxygenated hemoglobin
	Total hemoglobin concentration
	Oxygen level change

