### Statistical analysis

2.7.

We will perform descriptive statistical analysis of the general demographics of the study participants. We define completers as participants who finish 20 sessions of either intervention (VR-MAT or CT) and undergo measurements at 4 weeks of intervention. The statistical analysis will be conducted on an intention to treat basis and the last observation carried forward method will be used to complete the data. Adherence will be reported as the number of completers among enrolled participants. For neuropsychological assessments, a comparative analysis between two different intervention sequences (VC or CV) will be performed and the carry-over effects will be tested using *t*-tests on the change in each sequence for all crossover endpoints (70, 71). For variables with insignificant carry-over effects, the changes in variables during specific interventions from either sequence will be combined and compared. For patients with significant carry-over effects, we will compare the changes in specific interventions during the first period (20 sessions of either intervention). Comparisons between interventions will be performed using a two-tailed *t*-test or the Mann–Whitney *U* test, depending on normality. For music behavior responses obtained from the VR-MAT data, we will perform a two-way repeated-measures analysis of variance (ANOVA) on level (levels 1, 2, 3, and 4) and time (pre, day 8, day 15, and post) with Bonferroni *post-hoc* comparisons.

Repeated measures of correlation between executive function assessment and VR-MAT variables will be examined to determine the linear relationship between paired repeated data using the R package rmcorr from R.3.6.1 (72). The independent variables will remain the same for the analysis of fNIRS data, and the dependent variables will be the PRIs obtained from all channels. All analyses will be performed using the software package R.3.6.1,^1^ and the level of significance will be set to 0.05.

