## Discussion

3.

Instrumental music playing combined with VR technology might be a promising strategy for increasing the effectiveness of MAT by providing individualized and systematic interventions. This study aims to develop a replicable therapeutic protocol using an active music-playing platform. This topic is essential, considering that individuals need customized training programs suited to their functional levels and musical preferences. In addition, an increasing number of individuals require remote access to music-based attention programs, specifically those with restricted mobility. Moreover, our system can be used as a cognitive function measurement tool because music behavior data will be recorded with regard to accuracy and response time across all sessions. The data will be used to set up an individualized rhythm, determine whether to proceed to the next level of trial, and track changes over time.

The effectiveness of the system will be explored using cognitive outcome measures, including global and specific cognitive function test, especially executive function. Attention is a key component of executive function, as attention direct cognitive resources toward more important stimuli in order to sustain information processing and engaging and disengaging attention is linked to flexibility or inhibitory control [3; 4]. Thus, our cognitive outcomes could demonstrate how improvements in attentional abilities impact executive function, moreover global cognitive function. In addition, fNIRS data employ multifaceted variables of cerebral hemodynamics to indicate a PRI, which can provide interpretable information in terms of relationships and intensity changes over time. Therefore, the present study will contribute to increasing the scientific rigor of understanding how active music playing can affect cognitive function and cerebral hemodynamic responses, thus demonstrating its efficacy in cognitive rehabilitation. This specific study protocol enables music therapists to measure and quantify musical responses and clearly indicates how changes in musical responses are related to and can lead to cognitive enhancement. In addition, the evaluation and training protocols that we designed are readily applicable to music therapy in medical and rehabilitation settings if the use of electronic media and information technologies readily gains acceptance.

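### The VR-MAT evaluation labelled post (day 22) does not fit a 20-session, 4-week course, and the planned repeated-measures correlation on at most two paired visits does not remove average change

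*Protocol article*

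**What the plan says.** Study design sets the dose: "Each VR-MAT or CT training period will last 4 weeks with five 30-min intervention sessions per week, resulting in a total of 20 sessions". The Abstract agrees: "VR-MAT will take place five times weekly over 4 weeks".

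Section 2.3.1 (VR-MAT behavioral data) places the performance evaluations at "pre (day 1), mid1 (day 8), mid2 (day 15), and post (day 22) sessions" and runs them without background music. Section 2.7 (Statistical analysis) uses the same four occasions as a factor in the level-by-time ANOVA: "time (pre, day 8, day 15, and post) with Bonferroni" post-hoc comparisons.

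Executive function follows a different calendar. Under Outcome measurement, "neuropsychological outcomes will be measured for each participant at baseline, after 20 sessions (4 weeks), and after 40 sessions of intervention", the last being at 8 weeks.

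Section 2.7 then links the two, naming the R package rmcorr: "Repeated measures of correlation between executive function assessment and VR-MAT variables will be examined to determine the linear relationship between paired repeated data". The Discussion states what the link is meant to show, saying that the protocol "clearly indicates how changes in musical responses are related to and can lead to cognitive enhancement".

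The article does not define day, and it gives no rule for matching the two schedules.

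**The concern.** There are two separate problems.

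The first is timing. An evaluation called post should follow the course it evaluates. If it falls at the start of week 4, the pre-post change in accuracy and response time describes about three weeks of training while carrying the label of the whole course. Any pairing with the closing executive-function test would set drumming after 15 sessions against cognition after 20.

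The second is the choice of statistic, and it does not depend on which day the post evaluation falls. The Discussion is about whether a person's change in musical response goes with that person's change in cognition. With two visits per person, unadjusted rmcorr mixes this with the average change of the whole group. Practice on the drumming task, repeated cognitive testing, and recovery in patients who may be little more than 3 months from injury could all move both averages. A significant correlation could then arise without any link between individual changes.

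**Working it through.** **Timing**

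Inputs: 4 weeks and five sessions a week (Study design); evaluation days 1, 8, 15 and 22 (section 2.3.1); tests at baseline, 4 weeks and 8 weeks (Outcome measurement).

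1. The plan's own figure reproduces: 4 × 5 = 20 sessions.
2. Calendar-day reading. Put five weekday sessions in each week, starting on day 1. Days 1, 8, 15 and 22 are then the slots of sessions 1, 6, 11 and 16, whichever weekday the course starts on. Before day 22, 3 × 5 = 15 sessions are done, so 5 of 20 (25%) fall on or after the post evaluation. Session 20 falls on day 26 (Monday start) or day 28 (any other weekday start), 4 to 6 days after it.
3. Training-day reading. One pre day + 20 sessions + one post day = 22, which would put the post evaluation after the course. But 22 / 5 = 4.4 weeks, ending on calendar day 30 for a Monday start, against a stated 4 weeks. If days 8 and 15 are evaluation-only too, 22 − 4 = 18 training days remain, not 20.
4. Session-number reading. A 20-session course has no session 22.

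**Pairing** (calendar days, tests at about study days 0, 28 and 56)

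| Sequence | VR-MAT evaluations, study day | Days to nearest test |
|---|---|---|
| VC | 1, 8, 15, 22 | 1, 8, 13, 6 |
| CV | 29, 36, 43, 50 | 1, 8, 13, 6 |

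The pre evaluation meets a test (baseline in VC, week 4 in CV). The two middle evaluations have no counterpart. The post evaluation can be matched only loosely with the closing test (week 4 in VC, week 8 in CV). That gives at most two pairs per person.

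**The statistic with two visits**

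1. rmcorr removes each participant's own mean. With two visits and changes dx and dy, the centred values are ±dx/2 and ±dy/2. The sum of products is Σdx·dy/2, and the sums of squares are Σdx²/2 and Σdy²/2.
2. Hence r = Σdx·dy / √(Σdx² · Σdy²), with N(k − 1) − 1 = 24 × 1 − 1 = 23 degrees of freedom. The mean changes are not subtracted.
3. If individual changes are independent, with means a and b in units of the SD of change, r is close to ab / √((1 + a²)(1 + b²)). For a = b = 0.5 this is 0.25 / 1.25 = 0.20. For 0.8 it is 0.64 / 1.64 = 0.39. For 1.0 it is 1 / 2 = 0.50.
4. Simulated rate of two-sided p < 0.05 with independent normal changes. The article gives no mean changes, so a and b are assumptions. N = 24 is the recruitment target; N = 19 is 24 × 0.8 = 19.2 after the 20% attrition it allows for.

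| Mean gains (SD of change) | Mean r | rmcorr, N = 24 | rmcorr, N = 19 | Mean-centred changes |
|---|---|---|---|---|
| 0 and 0 | 0.00 | 5% | 5% | 5% |
| 0.3 and 0.3 | 0.08 | 7% | 6% | 5% |
| 0.5 and 0.5 | 0.20 | 16% | 13% | 5% |
| 0.8 and 0.8 | 0.39 | 52% | 41% | 5% |
| 1.0 and 1.0 | 0.50 | 79% | 68% | 5% |
| 1.0 and 0.2 | 0.14 | 10% | 9% | 5% |

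**The case against.** - **Day is undefined.** The article separates evaluation from training sessions, and the program's first screen has a Day field, so a count of training days is possible and would put the post evaluation after training. This stands to the extent that a reader should not infer that the last week is certainly missed. But 22 training days do not fit the stated 4 weeks, so the sections conflict on this reading too.
- **Later data exist.** The Discussion says that accuracy and response time are logged throughout, and section 2.7 correlates VR-MAT variables without restricting them to the four evaluations. It would therefore be wrong to say that nothing is observed in week 4 or that nothing can be paired with the closing test. The limit is comparability: training uses background music and the evaluations do not.
- **The inflation has nothing to do with day 22.** Correct. Moving the post evaluation leaves every rate in the second table unchanged. The timing problem is sized only by the 5 of 20 sessions; its effect on any result cannot be estimated from the article.
- **The high rates need large, equal gains.** Also correct. VR-MAT is the trained task and transfer to executive function may be small; gains of 1.0 and 0.2 SD give about 10%. At 0.5 SD each, about 84% of trials would show nothing significant.
- **rmcorr answers its own question.** It estimates a common within-person association, section 2.7 promises only a linear relationship, and the Abstract calls this exploration. The rates above are errors only against the null of unrelated individual changes. That null is the relevant one for the claim in the Discussion.
- **This is detail for a full protocol or SAP.** A pairing rule could be left there. The evaluation days and the named method, however, are fixed in the article.

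**Conclusion.** The point holds in two parts.

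First, the evaluation days and the length of the course must be reconciled on any reading. On the natural one, the post evaluation comes after 15 of 20 sessions, the ANOVA's pre-post contrast leaves out a quarter of the training, and the evaluation misses the closing executive-function test by 4 to 6 days and one training week in both sequences.

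Second, unadjusted rmcorr on two visits cannot separate linked individual change from average change. The rate of significant results with unrelated changes runs from close to the nominal 5% to 79% at N = 24, depending on mean changes that the article does not give. The calculation assumes two pairs per person and independent normal changes.

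A reader might infer that rmcorr cannot be run, that it would necessarily report a spurious link, or that the comparison of VR-MAT with conventional training is compromised. The article supports none of these. The analysis can be run with loosely matched pairs, the inflation is small if either measure changes little on average, and the comparison between interventions uses the neuropsychological tests on their own schedule. This is a matter for the secondary, mechanistic results of a pilot. It should be changed.

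**What to change.** 1. Define day. Schedule and label the post evaluation after session 20, at the neuropsychological visit that closes the VR-MAT period: week 4 in sequence VC, week 8 in CV. Use the same label for the ANOVA time factor.
2. Define the correlation pairs as the start and the end of the VR-MAT period. Replace unadjusted rmcorr with the correlation of change in VR-MAT with change in executive function (Pearson or Spearman), or with a mixed model containing a fixed visit effect. The two middle evaluations stay in the ANOVA.
3. If training-session recordings are to be used in the correlation, say so and keep them apart from the evaluation data.

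The cost is small: one evaluation moves by a few days and a sentence or two of analysis text changes, with no extra assessments or participants. The reported correlation may be smaller.

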#### Equipment set-up

2.3.2.

All musical stimuli will be generated using Logic Pro X (Apple Inc., California, United States) and combined with the visual stimuli using Unity (Unity Technologies, San Francisco, United States). The electronic drum consists of tom-toms on an adjustable stand, which is connected to a screen, speakers, and a desktop computer. A total minimum area of two meters squared will be required to set up the tom-toms on the stand, including space for the participant to sit (Figure 4).

**Figure 4 fig4:**
[figure not shown]
**(A)** Example of equipment set-up. A control panel of the electronic drum is connected to a desktop computer and a monitor. Accompaniment and sound feedback will be provided via a headphone that is connected to the control panel. **(B)** An individual demonstrating VR-MAT.

### Conventional cognitive training

2.4.

The CCT was designed to mimic attention process training, which has proven to be effective in patients with ABI(48, 49). Therefore, the CCT encompasses various levels of attention, such as focused, sustained, selective, alternating, and divided attention, and progresses with the participants’ levels. The training difficulty level is adjusted by modifying tasks, such as altering the number of presented stimuli. Feedback is provided after each task, and the therapist provides a summary at the end of each session. The CCT is administered by an experienced occupational therapist, utilizing diverse training methods including cards, dictation, buzzer, paper-and-pencil tasks, or computerized cognitive training.

### Outcome measurement

2.5.

Baseline demographic characteristics, including sex, age, diagnosis of ABI, duration after ABI, side of brain lesion, and education, will be collected. Additionally, neuropsychological outcomes will be measured for each participant at baseline, after 20 sessions (4 weeks), and after 40 sessions of intervention (after 20 sessions of alternative intervention; 8 weeks) by a blinded neuropsychologist. We will collect data on neuropsychological outcomes in two ways: global cognitive function and executive function, which are specific targets of VR-MAT. All of the cognitive function tests will be administered in Korean. Additionally, we will obtain VR-MAT behavioral data, which is previously explained, and functional infrared spectroscopy (fNIRS) data (Table 1).

**Table 1 tab1:** List of outcome measurements.

Global neuropsychological assessment	Mini-mental status examination (MMSE)
Clinical dementia rating (CDR)
Global deterioration scale (GDS)
Subjective memory complaint questionnaires (SMCQ)
Executive function assessment	Trail making test (TMT)
	TMT-black & white (TMT-B&W)
	Attention-switching Task (AST)
	Stop signal task (SST)
	Spatial working memory (SWM)
VR-MAT behavioral measures	VR-MAT response time
	VR-MAT accuracy
Functional near-infrared spectroscopy	Oxygenated hemoglobin
	Deoxygenated hemoglobin
	Total hemoglobin concentration
	Oxygen level change

#### Global neuropsychological assessment

2.5.1.

We will administer the mini-mental status examination (MMSE) (48), clinical dementia rating (CDR) (49), and global deterioration scale (GDS) (50) for the global cognitive functions and subjective memory complaint questionnaires (SMCQ) (51) for subjective cognitive function by an experienced research neuropsychologist. The MMSE is the most widely used screening tool for cognitive deficits. It comprises 30 items that provide information about orientation for time and place, memory (encoding and delayed recall), attention, calculation, language, and visuospatial construction. The CDR is a semi-structured informant-based clinical interview that rates global cognitive performance and functioning. It comprises six domains (memory, orientation, judgment and problem-solving, community affairs, home and hobbies, and personal care) (49). The global CDR score (range 0–3) will be calculated using an established algorithm indicating dementia severity: 0, no dementia; 0.5, questionable dementia; 1, mild dementia; 2, moderate dementia; and 3, severe dementia. The CDR sum of the box (CDR-SOB; range, 0–18) will be obtained as the sum of each domain score. A higher global CDR or CDR-SOB score indicates a greater severity of dementia. The Korean version of the CDR has also been validated (52). The GDS, which emphasizes memory function and the ability to complete activities of daily living, is used to rate the severity of cognitive deterioration in seven stages ranging from “no global impairment” (stage 1) to “very severe global impairment” (stage 7). Stages 1–3 indicate pre-dementia and stages 4–7 represent dementia (8). In addition, we will measure subjective cognitive function (beliefs about one’s own memory) using a 14-item of SMCQ (subjective memory complaint questionnaire). The total SMCQ score ranges from 0 to 14, with higher scores indicating more severe subjective cognitive decline (51).

